### Sample size

We will recruit 108 participants (54 per group and per site). Feasibility studies do not include formal sample size calculations [56], but experts recommend 12–36 per arm [59, 60]. We will enroll 27 participants per arm per site. This sample will give a 95% CI of width ≤ 0.34 for the difference in group proportions, assuming attrition is ≤ 0.4 in the control group. A sample size of 54 per arm will also allow 95% CIs of width ≤ 0.29 for other outcomes (e.g., proportion recruited). The sample size calculation for our future definitive RCT will be based on data from this feasibility study.

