### Data analyses

To inform any modifications before our definitive RCT, we will compare study data to pre-set feasibility criteria (Table 2). For objective 1 (measuring acceptability), we will perform a theoretically informed analysis of interview data using the Theoretical Framework of Acceptability (TFA; [96]). Our theoretically informed analysis situates the professional knowledge of the researcher, allows transparent examination of the research by the reader, and has two main characteristics: how data are structured and how data are interpreted [97]. The structure of our analytic process will be anchored in the theoretical framework. We will interpret the meaning of participants’ words vis-à-vis the theory while allowing new themes to develop. Our analysis will begin after the first interview and be ongoing during the study. RCs at each site will conduct initial coding, using TFA as a guide to structure themes while remaining open to identifying new themes, with line-by-line analysis. Initial findings will be shared with our SSC for review and discussion, then applied to the full data set. In analyzing the full data set, we will remain open to identifying new themes not accounted for in the TFA, reflecting our sensitive use of theory to guide analysis. For rigor and transparency, we will complete the Consolidated Criteria for Reporting Qualitative Research (COREQ) [98].

**Table 2 Tab2:** Acceptability and study rigor and conduct data, with thresholds for assessing feasibility of future definitive randomized controlled trial

Methodological issues	Comments^a^	Feasibility data^a^	Criteria^b^	Feasible? (Y/N)	Need to modify pre-RCT? (Y/N)
1.Was the Family Navigation intervention acceptable to children and caregivers based on the 7 domains from the Theoretical Framework of Acceptability (TFA), including: a. Affective attitude b. Burden c. Perceived effectiveness d. Ethicality e. Intervention coherence f. Opportunity costs g. Self-efficacy	(e.g., data from 1-on-1 interviews)	(e.g., data will be analyzed using thematic analysis, which precludes quantification; 7 themes, plus additional sub-themes)	For each of the 7 domains, findings will be reviewed, discussed, and interpreted with our Stakeholder Committee and research team to determine whether parts of the Family Navigation intervention should remain unchanged or if changes are needed before implementing in our definitive RCT	(e.g., “yes” for all 7 domains)	(e.g., “yes” for 1 domain; “no” for 6 domains)

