2.What proportion of participants approached were eligible?			≥ 90% approached were eligible		
3.Did recruited participants complete consent/assent procedures?			≥ 95% recruited participants completed consent/assent procedures		
4.Did recruitment lead to successful enrollment?			100% sample size goal achieved		
5.Did participants agree to randomization?			≥ 95% participants agreed to be randomized		
6.Did randomization yield equality across groups?			Equal numbers of participants randomized to experimental and control groups		
7.Were blinding procedures effective?			100% analysts remained blinded to group assignment		
8.Were outcome assessments completed?			≥ 95% participants retained in the study completed outcome assessments		
9.How complete were outcome assessments at all study measurement intervals?			≥ 95% outcome assessments were complete		
10. Were outcome assessments burdensome for families?			≥ 90% children and caregivers disagreed that outcome assessments were burdensome		
11. Was study protocol acceptable to children and caregivers?			≥ 90% children and caregivers agreed study protocol was acceptable		
12. Was the level of attrition adequate within experimental (Family Navigation + Usual Care) and control (Usual Care only) groups at 12 months?			Experimental (FN + UC): 15–25% attrition Control (UC): 30–40% attrition		
13. Was collection of attrition data adequate to calculate sample size for definitive RCT?			≥ 95% participants had attrition data collected by 12 months post-baseline		
14. Were logistics of running a multi-center trial assessed?			Review procedures (ongoing and end-of-grant) with investigators, research staff, navigators		
15. Did all components of the protocol work together adequately?			Review procedures (ongoing and end-of-grant) with investigators, research staff, navigators		

^a^Comments and Feasibility Data columns will be populated with study data collected during our study; example provided for context

^b^Criteria column thresholds based on objective criteria (when possible) and experience gained through study implementation as well as data analysis and interpretation with Stakeholder Committee and research team

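### Table 2 row 12 scores attrition against two-sided bands that 54 per arm will usually miss by chance, and its floor on the FN arm counts very low attrition as a miss

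*Protocol article*

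**What the plan says.** The Data analyses section states that "we will compare study data to pre-set feasibility criteria (Table 2"), so that changes can be made before the definitive RCT. Table 2 has separate yes/no columns for feasibility and for the need to modify. Row 12 asks: "Was the level of attrition adequate within experimental (Family Navigation + Usual Care) and control (Usual Care only) groups at 12 months"? Its criterion, for FN plus usual care and then for usual care, is "15–25% attrition Control (UC): 30–40% attrition". The row gives no tolerance, interval rule or one-sided reading. Footnote b describes the basis of the thresholds: "Criteria column thresholds based on objective criteria (when possible) and experience gained through study implementation", together with interpretation by the Stakeholder Committee and research team.

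The Sample size section fixes the numbers: "We will recruit 108 participants (54 per group and per site"). It promises a "95% CI of width ≤ 0.34 for the difference in group proportions", assuming control attrition of at most 0.4. It adds: "A sample size of 54 per arm will also allow 95% CIs of width" at most 0.29 for other outcomes. The Trial interventions section says that FN is meant to reduce attrition. The Data analyses section names attrition yes/no at 12 months as the primary outcome.

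**The concern.** There are two problems with the row as worded.

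- **Width.** Each band is 10 percentage points wide. A single arm of 54 gives a 95% CI of roughly 21–25 points at these rates. An observed percentage can easily fall outside its band when the true rate sits at the centre, and both arms must land inside together.
- **Direction.** Rows 2, 3, 5, 8–11 and 13 are floors in the favourable direction. Row 12 also has limits on the favourable side. FN attrition of 10% is outside the criterion although lower attrition is the purpose of FN. Control attrition of 45% is outside it too, although that leaves more room for FN to help.

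Row 12 is the only pre-set threshold on the level of attrition; row 13 concerns only whether attrition data were collected. If it usually reads no by chance, and nearly always when FN does very well, the row tells the team little about whether to go forward or modify.

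**Working it through.** **Inputs.** n = 54 per arm (Sample size). Bands of 15–25% for FN and 30–40% for UC (Table 2, row 12). True rates of 20% and 35% are the band midpoints; they are my assumption, as the article does not name them as expected values.

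**The plan's own precision figures.**
- Difference, Wald width: 2 × 1.96 × √(0.40×0.60/54 + 0.20×0.80/54) = 0.337. This agrees with the stated ≤ 0.34 when FN attrition is 20%.
- Single proportion at its widest (p = 0.5): 2 × 1.96 × √(0.25/54) = 0.267 by Wald and 0.278 by the exact method. Both are within the stated ≤ 0.29.
- Single arm at 20%: 2 × 1.96 × √(0.20×0.80/54) = 0.213. At 35%: 2 × 1.96 × √(0.35×0.65/54) = 0.254. The bands are 0.10 wide.

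**Bands as event counts.** FN: 0.15×54 = 8.1 and 0.25×54 = 13.5, so 9–13 events. UC: 0.30×54 = 16.2 and 0.40×54 = 21.6, so 17–21 events.

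**Chance of meeting the row as written** (exact binomial, arms independent):
- Truth 20%/35%: P(9–13) = 0.601 and P(17–21) = 0.523. The product is 0.315, so the row fails 69% of the time.
- Across true rates inside both bands, the joint probability runs from 0.16 to 0.31. A search over all true rates finds nothing higher than about 0.315, so mid-band is in effect the best case.
- Truth 10%/35%: P(9–13) = 0.086, and 0.086 × 0.523 = 0.045. The FN estimate falls below 15% with probability 0.914.

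**Sensitivity to reading.**
- Rounded to whole percent, 8/54 (14.8%) and 16/54 (29.6%) count as inside. At 20%/35% this gives 0.694 × 0.607 = 0.421, so 58% failure. At 10%/35%, P(8–13) = 0.167, and 0.167 × 0.607 = 0.101.
- With 51–53 evaluable per arm and unrounded percentages, failure at mid-band is 57–67%.
- Keeping both bands and passing 80% of the time at mid-band would need about 196 per arm.

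**One-sided limits on the point estimates** (FN ≤ 13 of 54, UC ≥ 17 of 54):

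| Truth FN/UC | P(FN met) | P(UC met) | Both |
|---|---|---|---|
| 20%/35% | 0.823 | 0.751 | 0.62 |
| 15%/40% | 0.974 | 0.923 | 0.90 |
| 10%/35% | 0.999 | 0.751 | 0.75 |
| 25%/25% | 0.511 | 0.172 | 0.09 |
| 30%/30% | 0.214 | 0.457 | 0.10 |
| 35%/35% | 0.059 | 0.751 | 0.04 |

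The present bands, at the same three equal-rate scenarios, are met 0.08, 0.08 and 0.03 of the time. Little discrimination is lost.

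**The case against.** The strongest reply is that little hangs on the row. A reader might infer that a miss would declare the trial infeasible, stop progression, or distort the size of the definitive RCT. The article supports none of these. No stop or overall verdict is tied to row 12. Feasibility and need to modify are scored separately, and footnote b brings in interpretation by the committee. The Data analyses section bases the power calculation on the 95% CI for attrition, not on the band. This reply stands, and it limits the severity.

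It does not rescue the row. Footnote b says what the thresholds rest on; it gives no rule for a miss. A pre-set criterion that is usually missed, and then explained afterwards, does little work.

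A second reply is that the bands check planning assumptions. Control attrition of 30–40% is what the Background calls common, and the Sample size section assumes at most 0.4. That is a fair reason to discuss UC attrition above 40%. It is not a reason to score it as inadequate, and it does not justify a floor under FN.

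A third reply is that 69% depends on unrounded percentages. That is correct, and the range is therefore given as 58–69%. Under every reading checked, failure remains more likely than not at mid-band.

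**Conclusion.** The point holds as a should-fix. At 54 per arm, row 12 is met about 31% of the time when the truth is mid-band (about 42% with rounding), and hardly more often at any other true rates. At a true FN rate of 10% with UC at 35%, it is met 4.5% of the time (about 10% with rounding), so the row penalises FN for doing what it is meant to do. These figures assume independent arms, binomial counts, 54 evaluable per arm, and that both observed percentages must lie in their bands, which is the natural reading of the table. The consequence is a misleading feasibility flag on the level of the primary outcome. Estimation of attrition and the sizing of the RCT are unaffected.

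**What to change.** Restate the row 12 criterion as one-sided limits on the point estimates, using numbers already in the table: FN attrition 25% or less (13 of 54 or fewer) and UC attrition 30% or more (17 of 54 or more). Report each arm's 95% CI beside the result. State that FN attrition below 15% is not a failure. State that UC attrition above 40% is noted for discussion as a departure from the assumption in the Sample size section, but is not scored as a failure.

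Do not add a rule that downgrades the result to review whenever an arm's 95% CI spans its limit. At 54 per arm, a clear pass would then need about 7–8 or fewer FN events and 23–24 or more UC events, depending on the interval method. That happens 1–2% of the time at 20%/35% and 13–17% at 15%/40%.

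The cost is one table row, with no change to sample size, data collection or care. It can be made before the quantitative analysis, which takes place only at study completion. Two drawbacks remain. The row no longer fails on unexpectedly low FN or high UC attrition, though both are still reported. It also still fails 38% of the time at mid-band (1 − 0.62), which is a limit of the sample size that rewording cannot remove.

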### Ethical considerations

Children and caregivers can have emotional responses when discussing obesity-related issues. Our study takes place in multidisciplinary clinics, which include mental health professionals. Our study leaders ([name], JH, IZ) will work with research staff, navigators, clinicians, and administrative staff at our clinics to develop clear and specific processes to ensure children and caregivers are able to access mental health support (within or beyond our clinics, if relevant) when support is needed.

## Discussion

Attrition in managing pediatric obesity is a common occurrence. Families who attend more intervention sessions for obesity management and remain enrolled in care for longer achieve the greatest health improvements [100–103], observations that highlight the value of our study. We anticipate our findings will provide evidence that attrition has the potential to be reduced. The heterogeneity of approaches tested, small number of studies, sub-optimal study quality, and variable responses highlight the imperative for experimental research like ours to test evidence-based, theory-informed strategies such as FN that may reduce attrition in managing pediatric obesity. Our feasibility study represents a key next step in addressing obesity in children to help families get the most out of their care and optimizing the use of valuable health care resources.

### Knowledge translation

Our knowledge translation (KT) plan includes a blend of integrated and end-of-grant activities, which were informed using an established framework [104]. Children, caregivers, and clinicians from our SSC will partner with study leaders to co-author summaries of study results for our target audiences, providing real-world context for our findings and emphasizing key messages in plain language. Our integrated KT includes purposeful activities that are essential for study success, including formal meetings for our SSC and TSC, daily communication between research staff and clinicians, qualitative data analysis and interpretation that spans our project, and regular email correspondence to update stakeholders. Several of our team members lead multidisciplinary clinics for managing pediatric obesity, so study-related discussions and decisions will influence how our clinics plan and offer health services. We also lead provincial health system networks, with direct communication lines to enable province-level dissemination to clinicians and decision makers. Team members have established relationships with colleagues from Obesity Canada. We will share study data with public and professional audiences through newsletters and social media in the Obesity Canada community (> 50,000 members), with reach beyond academia and healthcare. At study completion, team members will work with public affairs experts at Obesity Canada and their respective institutions on press releases about findings. Results will be applied directly to inform our future definitive RCT to reduce attrition in pediatric obesity management.

### Trial oversight

Our TSC will meet at the start of our study and annually thereafter. TSC members include three arms-length, national research experts with backgrounds in pediatrics, obesity, clinical trials, and qualitative research who will form the committee with our three study leaders ([name], JH, IZ). Our TSC will review the study progress, approve the protocol and any amendments, and resolve any emerging challenges. A Data Safety and Monitoring Committee will not be established because the UAlberta Human Research Ethics Board views our study as a low-risk intervention.

### Trial status

Study activities were delayed due to the COVID-19 pandemic. Funding was received in July, 2021, preparatory study activities began in September, 2021, and participant recruitment began in October, 2022.

## Data Availability

The datasets generated and/or analyzed during the current study are not publicly available since participants will complete informed and written consent (or assent) procedures explaining that study data are confidential and will only be shared within our research team. Summary data are available from the corresponding author upon reasonable request.

## Abbreviations

AE: Adverse event
BMI: Body mass index
CANPWR: CANadian Pediatric Weight management Registry
CI: Confidence interval
CIHR: Canadian Institutes of Health Research
CONSORT: Consolidated Standards of Reporting Trials
EBCD: Experience-Based Co-Design
FN: Family Navigation
HRQoL: Health-related quality of life
HUI: Health Utility Index
KT: Knowledge translation
MI: Motivational interviewing
QALY: Quality-adjusted life years
RC: Research Coordinator
RCT: Randomized controlled trial
SPIRIT: Standard Protocol Items: Recommendations for Interventional Trials
SSC: Stakeholder Steering Committee
TFA: Theoretical Framework of Acceptability
TSC: Trial Steering Committee
